#### 4.1.1.7

##### **Characterization of Motor Function and Potential Transition States to Parkinson's Disease in LRRK2 mutation Carriers and Controls.**

Gait disturbances play a major role in the motor manifestation of PD. Traditional assessments aimed at measuring motor deficits, including the UPDRS, do not identify subtle differences in individuals at risk for PD, while quantitative measures have shown promise in this. Thus, some investigators reason that more sensitive tests of motor function are needed to increase the likelihood of identifying pre-diagnosis motor changes. Quantitative measures of gait and mobility should provide a means for assessing pre-diagnosis changes.

Researchers at Tel Aviv Medical Center have completed preliminary work supporting the potential of using quantitative measures of gait and mobility as a means for assessing pre-diagnosis changes. The current sub-study will build on this preliminary work and involve a protocol to obtain longitudinal motor function data at a subset of PPMI sites. A short motor assessment will be administered using a gait system that includes 3 lightweight wireless wearable sensors. The system measures acceleration of movement in 3 orthogonal axes as a function of time. It is anticipated that longitudinal data from this protocol will provide insight into phenoconversion and pre-clinical motor symptoms and inform on dynamic changes of function throughout disease and potential modifiers and mediators of motor symptoms. Refer to the PPMI Characterization of Motor Function and Potential Transition States to Parkinson's Disease in LRRK2 mutation Carriers and Controls companion protocol.

#### 4.1.1.8

##### **Passive monitoring of individuals through wearable sensors or non-invasive objective measure (Sensor-PPMI).**

This observational study will determine the feasibility and value of using multiple wearable sensors (e.g., watch, wearable sensors or other non-

invasive measures) to identify clinical and sub-clinical characteristics (e.g., changes in activity, movement, sleep, socialization) that are present in participants with PD across the spectrum of disease severity as well as among individuals with possible prodromal Parkinson disease based on either symptoms (e.g., hyposmia and/or RBD) or genetic status (e.g., LRRK2 and GBA mutation carriers). Participants at centers with individuals with prodromal PD, PD and healthy controls will undergo their standard assessments as part of the PPMI study. In addition, they may be provided a watch or other non-invasive device for use for the duration of the study and asked to wear sensors or another type of non-invasive device on their limbs and trunk. The watch, sensor or device will be worn as frequently as desired by participants but ideally most of the time (including while sleeping). Participants will wear the watch and/or sensors or device during their in-person PPMI assessments and may have at least the examination portion of such visits video recorded.

A group of age matched healthy control subjects from the PPMI cohort may also participate in order to evaluate differences between these groups. At the study's conclusion, participants will complete a survey about their experiences in the study. Passive monitoring in PPMI may include more than one sub-study to evaluate devices. Refer to the **Passive monitoring of individuals through wearable sensors or non-invasive methods (Sensor-PPMI sub-study)** companion protocol for further details.

## **4.2. Selection of Study Population**

### **4.2.1. Inclusion Criteria (Parkinson Disease Subjects)**

- 4.2.1.1. Patients must have at least two of the following: resting tremor, bradykinesia, rigidity (must have either resting tremor or bradykinesia); OR either asymmetric resting tremor or asymmetric bradykinesia.
- 4.2.1.2. A diagnosis of Parkinson disease for 2 years or less at Screening.
- 4.2.1.3. Hoehn and Yahr stage I or II at Baseline.
- 4.2.1.4. Not expected to require PD medication within at least 6 months from Baseline.
- 4.2.1.5. Male or female age 30 years or older at time of PD diagnosis.
- 4.2.1.6. Confirmation from imaging core that screening dopamine transporter SPECT scan is consistent with dopamine transporter deficit (or for sites where DaTSCANTM is not available that VMAT-2 PET scan is consistent with VMAT deficit).
- 4.2.1.7. Ability to provide written informed consent in accordance with Good Clinical Practice (GCP), International Conference on Harmonization (ICH), and local regulations.
- 4.2.1.8. Willing and able to comply with scheduled visits, required study procedures and laboratory tests.
- 4.2.1.9. Women may not be pregnant, lactating or planning pregnancy during the course of the study.

- Includes a negative urine pregnancy test on day of Screening scan prior to injection (DaTSCANTM and/or F-AV-133).
  - Includes a negative serum pregnancy test prior to Screening scan injection (F-AV-133 only).
- 4.2.1.10. Women participating in VMAT-2 PET imaging must be of non-childbearing potential **or** be using a highly effective method of birth control 14 days prior to until at least 24 hours after injection of F-AV-133).
- Non-child bearing potential is defined as a female that must be either postmenopausal (no menses for at least 12 months prior to Screening) or surgically sterile (bilateral tubal ligation, bilateral oophorectomy or hysterectomy).
  - Highly effective method of birth control is defined as practicing at least one of the following: A birth control method that results in a less than 1% per year failure rate when used consistently and correctly, such as oral contraceptives for at least 3 months prior to injection, an intrauterine device (IUD) for at least 2 months prior to injection, or barrier methods, e.g., diaphragm or combination condom and spermicide. Periodic abstinence (e.g. calendar, ovulation, symptothermal, post-ovulation methods) is not acceptable.

#### **4.2.2. Exclusion Criteria (Parkinson Disease Subjects)**

- 4.2.2.1. Atypical PD syndromes due to either drugs (e.g., metoclopramide, flunarizine, neuroleptics) or metabolic disorders (e.g., Wilson's disease), encephalitis, or degenerative diseases (e.g., progressive supranuclear palsy).
- 4.2.2.2. Currently taking levodopa, dopamine agonists, MAO-B inhibitors (e.g., selegiline, rasagiline), amantadine or other PD medication.
- 4.2.2.3. Has taken levodopa, dopamine agonists, MAO-B inhibitors or amantadine within 60 days of Baseline.
- 4.2.2.4. Has taken levodopa or dopamine agonists prior to Baseline for more than a total of 60 days.
- 4.2.2.5. A clinical diagnosis of dementia as determined by the investigator (Appendix 1).
- 4.2.2.6. Received any of the following drugs that might interfere with dopamine transporter SPECT imaging: Neuroleptics, metoclopramide, alpha methyl dopa, methylphenidate, reserpine, or amphetamine derivative, within 6 months of Screening.
- 4.2.2.7. Subjects participating in VMAT-2 PET imaging have received any of the following medications that might interfere with F-AV-133 PET imaging: neuroleptics, metoclopramide, alpha methyl dopa, methylphenidate, reserpine, or amphetamine derivative, within 2 weeks prior to the Screening F-AV-133 injection.
- 4.2.2.8. Current treatment with anticoagulants (e.g., coumadin, heparin) that might preclude safe completion of the lumbar puncture.

- 4.2.2.9. Condition that precludes the safe performance of routine lumbar puncture, such as prohibitive lumbar spinal disease, bleeding diathesis, or clinically significant coagulopathy or thrombocytopenia.
- 4.2.2.10. Any other medical or psychiatric condition or lab abnormality, which in the opinion of the investigator might preclude participation.
- 4.2.2.11. Use of investigational drugs or devices within 60 days prior to Baseline (dietary supplements taken outside of a clinical trial are not exclusionary, e.g., coenzyme Q10).
- 4.2.2.12. Previously obtained MRI scan with evidence of clinically significant neurological disorder (in the opinion of the Investigator).

#### **4.2.3. Inclusion Criteria (Healthy Control Subjects)**

- 4.2.3.1. Male or female age 30 years or older at Screening.
- 4.2.3.2. Ability to provide written informed consent in accordance with Good Clinical Practice (GCP), International Conference on Harmonization (ICH), and local regulations.
- 4.2.3.3. Willing and able to comply with scheduled visits, required study procedures and laboratory tests.
- 4.2.3.4. Women may not be pregnant, lactating or planning pregnancy during the course of the study.
  - Includes a negative urine pregnancy test on day of Screening scan prior to injection (DaTSCANTM and/or F-AV-133).
  - Includes a negative serum pregnancy test prior to Screening scan injection (F-AV-133 only).
- 4.2.3.5. Women participating in VMAT-2 PET imaging must be of non-childbearing potential **or** be using a highly effective method of birth control 14 days prior to until at least 24 hours after injection of F-AV-133).
  - Non-child bearing potential is defined as a female that must be either postmenopausal (no menses for at least 12 months prior to Screening) or surgically sterile (bilateral tubal ligation, bilateral oophorectomy or hysterectomy).
  - Highly effective method of birth control is defined as practicing at least one of the following: A birth control method that results in a less than 1% per year failure rate when used consistently and correctly, such as oral contraceptives for at least 3 months prior to injection, an intrauterine device (IUD) for at least 2 months prior to injection, or barrier methods, e.g., diaphragm or combination condom and spermicide. Periodic abstinence (e.g. calendar, ovulation, symptothermal, post-ovulation methods) is not acceptable.

#### **4.2.4. Exclusion Criteria (Healthy Control Subjects)**

- 4.2.4.1. Current or active clinically significant neurological disorder (in the opinion of the Investigator).
- 4.2.4.2. First degree relative with idiopathic PD (parent, sibling, child).
- 4.2.4.3. MoCA score of 26 or less (i.e., eligible if score is 27 to 30).
- 4.2.4.4. Received any of the following drugs that might interfere with dopamine transporter SPECT imaging: Neuroleptics, metoclopramide, alpha methyl dopa, methylphenidate, reserpine, or amphetamine derivative, within 6 months of Screening.
- 4.2.4.5. Subjects participating in VMAT-2 PET imaging have received any of the following medications that might interfere with F-AV-133 PET imaging: neuroleptics, metoclopramide, alpha methyl dopa, methylphenidate, reserpine, or amphetamine derivative, within 2 weeks prior to the Screening F-AV-133 injection.
- 4.2.4.6. Current treatment with anticoagulants (e.g., coumadin, heparin) that might preclude safe completion of the lumbar puncture.
- 4.2.4.7. Condition that precludes the safe performance of routine lumbar puncture, such as prohibitive lumbar spinal disease, bleeding diathesis, or clinically significant coagulopathy or thrombocytopenia.
- 4.2.4.8. Any other medical or psychiatric condition or lab abnormality, which in the opinion of the investigator might preclude participation.
- 4.2.4.9. Use of investigational drugs or devices within 60 days prior to baseline (dietary supplements taken outside of a clinical trial are not exclusionary, e.g., coenzyme Q10).
- 4.2.4.10. Previously obtained MRI scan with evidence of clinically significant neurological disorder (in the opinion of the Investigator).

#### **4.2.5. Inclusion Criteria (SWEDD Subjects)**

See Section 4.2.1 for Inclusion Criteria for PD subjects. All criteria apply except a SWEDD subject must have confirmation from imaging core that screening dopamine transporter SPECT scan shows no evidence of dopamine transporter deficit (or for sites where DaTSCAN™ is not available that VMAT-2 PET scan shows no evidence of VMAT deficit).

#### **4.2.6. Exclusion Criteria (SWEDD Subjects)**

See Section 4.2.2 for Exclusion Criteria for PD subjects which also apply to SWEDD subjects.

#### **4.2.7. Inclusion Criteria (Prodromal Subjects)**

- 4.2.7.1. Subjects must have at least one of the following characteristics:
  - Hyposmia:*
    - a) Male or female age 60 years or older
    - b) Confirmation from olfactory core that olfaction as determined by UPSIT is at or below the 10th percentile by age and gender
  - REM Behavior Disorder (RBD):*

- a) Male or female age 60 years or older
  - b) Confirmation from sleep core that subject's Polysomnography (PSG) meets criteria for RBD and/or clinical diagnosis of RBD by site investigator including existing PSG.
- 4.2.7.2. Confirmation from imaging core that screening dopamine transporter SPECT scan (or V-MAT-2 PET scan for sites where DaTSCAN™ is not available) is read as eligible (see below)
- About 80 subjects will have a range of DAT deficit similar to subjects with early PD (mild to moderate DAT deficit). About 20 subjects will be selected with no DAT deficit or minimal DAT deficit similar in age, gender, and risk profile to those with mild to moderate DAT deficit.
- 4.2.7.3. Ability to provide written informed consent in accordance with Good Clinical Practice (GCP), International Conference on Harmonization (ICH), and local regulations.
- 4.2.7.4. Willing and able to comply with scheduled visits, required study procedures and laboratory tests.
- 4.2.7.5. Women may not be pregnant, lactating or planning pregnancy during the course of the study.
- Includes a negative urine pregnancy test on day of screening scan prior to injection (DaTSCAN™).
  - Includes a negative serum pregnancy test prior to Screening scan injection (F-AV-133 only).
- 4.2.7.6. Women participating in VMAT-2 PET imaging must be of non-childbearing potential **or** be using a highly effective method of birth control 14 days prior to until at least 24 hours after injection of F-AV-133).
- Non-child bearing potential is defined as a female that must be either postmenopausal (no menses for at least 12 months prior to Screening) or surgically sterile (bilateral tubal ligation, bilateral oophorectomy or hysterectomy).
  - Highly effective method of birth control is defined as practicing at least one of the following: A birth control method that results in a less than 1% per year failure rate when used consistently and correctly, such as oral contraceptives for at least 3 months prior to injection, an intrauterine device (IUD) for at least 2 months prior to injection, or barrier methods, e.g., diaphragm or combination condom and spermicide. Periodic abstinence (e.g. calendar, ovulation, symptothermal, post-ovulation methods) is not acceptable.

#### **4.2.8. Exclusion Criteria (Prodromal Subjects)**

- 4.2.8.1. Current or active clinically significant neurological disorder or psychiatric disorder (in the opinion of the Investigator).
- 4.2.8.2. GDS score greater than or equal to 10 (GDS score of 5 – 9 requires Investigator discretion to enter study).

- 4.2.8.3. STAI Form Y-1 greater than or equal to 54 requires Investigator discretion to enter study.
- 4.2.8.4. A clinical diagnosis of dementia as determined by the investigator (Appendix 1).
- 4.2.8.5. A clinical diagnosis of Parkinson disease at the Screening visit as determined by the Investigator.
- 4.2.8.6. Received any of the following drugs that might interfere with dopamine transporter SPECT imaging: Neuroleptics, metoclopramide, alpha methyl dopa, methylphenidate, reserpine, or amphetamine derivative, within 6 months of Screening.
- 4.2.8.7. Current treatment with anticoagulants (e.g., coumadin, heparin) that might preclude safe completion of the lumbar puncture.
- 4.2.8.8. Condition that precludes the safe performance of routine lumbar puncture, such as prohibitive lumbar spinal disease, bleeding diathesis, or clinically significant coagulopathy or thrombocytopenia.
- 4.2.8.9. Any other medical or psychiatric condition or lab abnormality, which in the opinion of the investigator might preclude participation.
- 4.2.8.10. Use of investigational drugs or devices within 60 days prior to Baseline (dietary supplements taken outside of a clinical trial are not exclusionary, e.g., coenzyme Q10).
- 4.2.8.11. Previously obtained MRI scan with evidence of clinically significant neurological disorder (in the opinion of the Investigator).

#### **4.2.9. Inclusion criteria (Genetic Cohort – PD Subjects)**

- 4.2.9.1. Patients must have at least two of the following: resting tremor, bradykinesia, rigidity (must have either resting tremor or bradykinesia); OR either asymmetric resting tremor or asymmetric bradykinesia
- 4.2.9.2. Parkinson disease diagnosis for 7 years or less at Screening
- 4.2.9.3. Hoehn and Yahr stage less than 4 at Baseline.
- 4.2.9.4. Male or female age 18 years or older at baseline.
- 4.2.9.5. Confirmation of causative LRRK2, GBA or SNCA mutation (willingness to undergo genetic testing as part of the prescreening or documentation of prior genetic testing results).
- 4.2.9.6. Ability to provide written informed consent in accordance with Good Clinical Practice (GCP), International Conference on Harmonization (ICH), and local regulations.
- 4.2.9.7. Willing and able to comply with scheduled visits, required study procedures and laboratory tests.
- 4.2.9.8. For subjects taking any of the following drugs (Neuroleptics, metoclopramide, alpha methyl dopa, methylphenidate, reserpine, or amphetamine derivative) must be willing and medically able to hold the medication for at least 5 half-lives before DaTSCANTM imaging.
- 4.2.9.9. Women who are pregnant or lactating will not undergo DaTSCANTM and/or F-AV-133 imaging assessments. (The imaging assessments that would have occurred during this time will be waived)

- Includes a negative urine (or serum if required by site) pregnancy test on day of Screening scan prior to injection (DaTSCANTM and/or F-AV-133).
  - Includes a negative serum pregnancy test prior to Screening scan injection (F-AV-133 only).
- 4.2.9.10. Women participating in VMAT-2 PET imaging must be of non-childbearing potential **or** be using a highly effective method of birth control 14 days prior to until at least 24 hours after injection of F-AV-133).
- Non-child bearing potential is defined as a female that must be either postmenopausal (no menses for at least 12 months prior to Screening) or surgically sterile (bilateral tubal ligation, bilateral oophorectomy or hysterectomy).
  - Highly effective method of birth control is defined as practicing at least one of the following: A birth control method that results in a less than 1% per year failure rate when used consistently and correctly, such as oral contraceptives for at least 3 months prior to injection, an intrauterine device (IUD) for at least 2 months prior to injection, or barrier methods, e.g., diaphragm or combination condom and spermicide. Periodic abstinence (e.g. calendar, ovulation, symptothermal, post-ovulation methods) is not acceptable.

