- 4.1.1.4 **PPMI Family History Substudy**, a companion protocol, will permit collection of family history from approximately 1200 Genetic Cohort subjects. The aim of the Family History Substudy is to identify individuals participating within the PPMI study who are related to each other so as to create family trees (pedigrees) which delineate the relationship among participating PPMI subjects. Subjects will be given a packet of study

materials approved by the Indiana University School of Medicine IRB. These materials contain a cover letter of introduction, a Consent Reply form with the PPMI subject ID inserted by the PPMI site coordinator, an Informed Consent form, an Authorization to Release Health Information for Research form (HIPAA) and a prepaid return envelope. The PPMI site will inform Indiana University by fax which PPMI subjects (by subject ID only) received the Family History packet. The Indiana University study team will contact subjects who provide informed consent to initiate the completion of the Family History Questionnaire. Refer to *The Parkinson's Progression Markers Initiative (PPMI) Family History Substudy* companion protocol.

4.1.1.5 **Prospective, longitudinal follow-up** of Parkinson's disease, vital status and assessment of life-long environmental exposure histories of PPMI subjects will be accomplished by subject participation in a registry entitled, *Follow-Up of Persons with Neurologic Disease (FOUND)-PPMI*. The registry will be managed by the University of California-San Francisco (UCSF) under their IRB approved protocol. PPMI subjects will be consented to allow the PPMI site to provide the subject's contact information to the UCSF study team, who will then contact subjects to invite them to undergo the informed consent process to join the registry (see section 9.2).

4.1.1.6 **PPMI Brain and Tissue Bank.** An important aspect of Parkinson's Disease research is post-mortem analysis of brain tissue and other types of tissue. Through this analysis, changes in the brain can be examined and correlated with motor, cognitive, and behavioral changes. Brain tissue will help Parkinson's Disease researchers further their understanding of the disease and its progression.

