## 7. Concomitant Medications

### 7.1.1. Initiation of PD Medications

It is anticipated that the majority of PD (and SWEDD) subjects will be able to remain off PD medications for at least 6 months after Baseline. However, PD medications may be initiated at any time after enrollment at the discretion of the patient or treating physician (inclusive of Prodromal and Genetic Cohort PD subjects). The medication used is at the discretion of the treating physician. It is anticipated that the majority of Genetic Cohort-PD and Registry-PD subjects may be on PD medications at baseline. If PD medications are to be initiated, subjects (except the Genetic Registry) will be asked to return for an ST

visit. The investigator will document any new medications or changes in medication at each study visit on the Concomitant Medication Log.

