### **14.2 Primary Objective**

To estimate the mean rates of change and the variability around the mean of clinical, imaging and biomic outcomes in early PD patients, and where appropriate to compare these rates between various subsets (including, but not limited to: early PD subjects vs. healthy subjects, PD vs. SWEDD, PD vs. Prodromal, PD with and without LRRK2, GBA or SNCA mutation, unaffected LRRK2, GBA or SNCA mutation carriers vs. healthy subjects) at study intervals ranging from 3 months to 36 months.

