### 14.4. Planned Analyses

Information summarizing planned analyses is described below. Further details regarding the analyses and plans for additional analyses will be contained in the PPMI Data Analysis Plan.

- 14.4.1. **Comparison of baseline characteristics among various subsets.** The first set of analyses will involve a comparison of baseline characteristics among the various subsets enrolled into the study. Continuous variables will be examined using a t-test and dichotomous variables will be examined using a chi-square test. Appropriate assumptions will be assessed for each comparison and any necessary adjustments (i.e., transformations) will be made prior to analysis. All analyses will be conducted at the 0.05 level.
- 14.4.2. **Comparison of short-term change in progression endpoints.** The second set of analyses will examine the short-term change during the first six months

for each progression endpoint. For continuous progression endpoints, the change over time will be modeled using a mixed model approach. For dichotomous progression endpoints, a logistic regression model will be fit. For each 'full' model of interest, an initial model will consist of all baseline characteristics, an indicator variable for whether the subject is a PD patient or healthy control, and all possible two-way interactions. We will utilize backwards selection to build a model for each progression endpoint.

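### PD with versus without a mutation compares groups that differ by design in duration, stage and treatment at entry, and the stated backwards selection protects none of these terms

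*Protocol*

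**What the plan says.** Section 14.2 (and 3.1) lists "PD with and without LRRK2, GBA or SNCA mutation" among the comparisons of rates of change, at study intervals of 3 to 36 months, so the clock starts at enrolment. Section 14.5 describes the contrast as genetic PD against early PD.

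The two groups enter under different rules:

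- **Duration.** Genetic Cohort PD (4.2.9): "Parkinson disease diagnosis for 7 years or less at Screening". Early PD (4.2.1): "A diagnosis of Parkinson disease for 2 years or less at Screening".
- **Stage.** Genetic Cohort PD: "Hoehn and Yahr stage less than 4 at Baseline". Early PD: "Hoehn and Yahr stage I or II at Baseline".
- **Treatment.** Section 7.1.1: "It is anticipated that the majority of Genetic Cohort-PD and Registry-PD subjects may be on PD medications at baseline". For early PD, current PD medication is an exclusion (4.2.2), and subjects must not be expected to need it for at least 6 months (4.2.1).

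Matching in 4.3 covers PD against healthy controls only. Section 14.4.2 puts all baseline characteristics and two-way interactions into an initial model for change over the first six months, then reduces it by backwards selection. Section 14.4.4 repeats the analyses for subsets of PD, which 3.1 allows to be defined by mutation. No term is named as retained.

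**The concern.** Duration, stage and treatment differ between the groups because the entry rules make them differ. They are also plausible determinants of the rates being compared. A selection rule that keeps or drops terms by their fit in the data does not guarantee that these three stay in. Where one group has no subjects at all, keeping them helps only through the assumed form of the model.

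What is at stake is attribution: a slower or faster rate in carriers could reflect later or treated disease. The effect can spread, because 14.4.3 carries forward only endpoints that differ between subsets, so a stage artefact could help a marker qualify.

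**Working it through.** **1. The protocol's own figures.** The means column of the table in 14.5 follows from d = (1.960 + 0.842) × √(1/n₁ + 1/n₂). With splits 150/150, 200/200, 300/150 and 400/200 this gives 0.3235, 0.2802, 0.2802 and 0.2426, against 0.33, 0.28, 0.28 and 0.24 printed. The table reproduces, but has no row for PD with versus without mutation. The same formula with 300 genetic PD and 400 early PD gives d = 0.214, or 0.247 after the protocol's 25% withdrawal (225 and 300).

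**2. Overlap at baseline.** By rule, early PD has nobody beyond 2 years since diagnosis, above stage II, or on PD medication at baseline. Genetic PD may have all three. If duration is uniform on 0 to 7 years (assumed; the protocol gives no distribution), 2/7 = 29%, or 86 of 300, fall within 2 years. For the rest there is no early PD comparator at baseline.

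**3. Effect of duration alone (illustration).** Section 1.1 cites an annual striatal loss of about 4% to 13% in PD. Assume the same constant fractional loss r in both groups and 2.5 extra years in genetic PD (the difference in midpoints, 3.5 − 1). Absolute annual loss then has the ratio (1 − r)^2.5:

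- r = 4%: 0.96^2.5 = 0.90, so 10% smaller.
- r = 13%: 0.87^2.5 = 0.71, so 29% smaller.

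Averaging over uniform durations of 0–2 and 0–7 years instead gives ratios of 0.906 (r = 4%), 0.785 (r = 10%) and 0.732 (r = 13%), so 9% to 27% smaller. On the proportional scale both groups lose r per year and the difference is zero.

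**4. What a given bias would do.** With SE = √(1/400 + 1/300) = 0.0764 SD, a residual bias of 0.1 SD (assumed) is 0.1/0.0764 = 1.31 standard errors. It raises the two-sided false-positive rate from 5% to about 26%, or about 20% with 25% withdrawal. The documents give no estimate of the bias, so this shows sensitivity and is not a forecast.

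**5. When the treatment contrast is sharpest.** It is largest early, before early PD subjects start medication, and the first six months are the window of 14.4.2. The examination with PD medication withheld is annual (6.1.1). The Genetic Cohort PD schedule has a repeat Part III at baseline and month 12 but none at month 6.

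**The case against.** Much of the case on the other side stands.

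- The comparisons are to be made where appropriate, and 14.5 calls this one exploratory.
- Adjustment is planned, because every baseline characteristic enters the initial model. Only retention is open.
- Early PD is untreated only at entry; 7.1.1 lets medication start at any time.
- Annual Part III scores are taken with medication withheld, and 1.1 reports no short-term regulatory effect of levodopa or agonists on DAT imaging. Treatment is therefore mainly a problem for clinical outcomes, a risk that 1.1 itself acknowledges.
- The 10% to 29% figure depends on scale. Section 1.1 quotes loss as an annual percentage, and on that scale the illustration gives no bias.

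These points limit the concern but do not remove it. The protocol does state a model-building rule, that rule protects no term, and initial adjustment cannot supply comparators that the entry criteria exclude.

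Two stronger readings are tempting. One is that a mutation effect cannot be separated from stage and treatment at all. That goes too far, given the planned adjustment and the overlapping subjects.

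The other is that relatives are analysed as independent, so that intervals are too narrow. The Family History Substudy aims to "identify individuals participating within the PPMI study who are related to each other", and 14.4.1 says "Continuous variables will be examined using a t-test and dichotomous variables will be examined using a chi-square test". But those tests concern baseline characteristics. Continuous rates use a mixed model, which can carry a family term, and 14.4 leaves detail to a Data Analysis Plan that is not shown. Family size and intraclass correlation are not given. Even with families of 2 to 3 and a correlation of 0.1 to 0.5 (assumed), the root design effect is 1.05 to 1.41, which makes intervals 1 − 1/1.05 = 5% to 1 − 1/1.41 = 29% too narrow if families are ignored. The effect is smaller here, where only one arm is clustered: standard errors are 2.8% to 25% larger. At 1.25 related carriers per family and a correlation of 0.2, the figure is 1.4%.

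**Conclusion.** The comparison is confounded by design in duration, stage and treatment at entry, and the stated selection rule does not protect against it. This follows from the entry criteria and 14.4 without any assumption. Its size is not known. The 10% to 29% difference in absolute imaging loss rests on constant fractional loss, 2.5 extra years and an absolute scale, and is zero on the proportional scale. For clinical outcomes the documents give no figure. The protocol does not support a claim that relatives are treated as independent or that intervals are too narrow. The point should be fixed for this contrast; it does not undermine the rate estimates within each cohort.

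**What to change.** In 14.4.2 to 14.4.4, for PD with versus without mutation:

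- Keep baseline disease duration and Hoehn and Yahr stage in the model, exempt from backwards selection.
- Report the contrast restricted to the baseline overlap: diagnosis 2 years or less, stage I or II, no PD medication at baseline.
- Add an analysis on time since diagnosis as a sensitivity analysis. Early PD reaches at most year 5 within the primary window (2 + 3 years), so later years need the longer follow-up.
- Handle on-study medication through the annual off-medication scores or a sensitivity analysis. Do not force it in as a covariate, since starting treatment can follow from progression.
- State whether imaging change is analysed on the absolute or the proportional scale.
- Optionally, where pedigree data exist, use a family random effect or family-clustered standard errors as a check. Pedigrees require separate consent to the substudy, so coverage may be incomplete.

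No new data are needed. The cost is precision in the restricted contrast. With 86 genetic PD (uniform duration, assumed) against 400, d = 2.802 × √(1/86 + 1/400) = 0.33, compared with 0.214 unrestricted. If only half of those 86 also met the stage and medication limits (assumed), 43 against 400 gives 0.45.
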